### Investigational Plan, Intervention, and Treatment Regimen

We will conduct a dose-escalation trial of lacosamide added to opioid therapy in patients with chronic abdominal pain owing to CP. Participants who meet all the inclusion criteria and none of the exclusion criteria will be included in this dose-finding study. We will use the Bayesian optimal interval (BOIN) [37,38] design to determine the MTD. The BOIN design received a fit-for-purpose designation from the FDA as a drug development tool [39]. The BOIN design is implemented in a simple manner similar to the traditional 3+3 design, but it is more flexible and possesses superior operating characteristics compared to those with more complex model-based designs, such as the continual reassessment method [40]. The target DLT rate for MTD is 0.3, and the maximum sample size is 24. We will enroll and treat patients in cohorts of size 3. The initial dose will be 50 mg taken orally twice a day (100 mg/day), followed by an incremental increase of 100 mg/day in 2 divided doses. The maximum daily dose of lacosamide will be 400 mg/day. The duration of lacosamide administration will be 7 days at each dose level. This target DLT rate and dose-escalation schedule were chosen based on previous trials that had suggested the efficacy and tolerability of comparable doses of lacosamide when used to treat partial seizures and painful diabetic neuropathy. Follow-up laboratory parameters (as obtained at study entry) will be obtained on day 8 (with a 3-day window) after therapy is completed. The trial design is illustrated in Figure 1 and is described as follows:

Patients in the first cohort are treated at dose level 1.To assign a dose to the next cohort of patients, dose escalation or de-escalation will be performed according to the rules displayed in Table 1.Repeat step 2 until the maximum sample size of 24 is reached or stop the trial if the number of patients treated at the current dose reaches 15.

In the BOIN design, the number of DLT is the number of patients with at least 1 DLT. When none of the actions (ie, escalation, de-escalation, or elimination) is triggered, the current dose remains unchanged for the next cohort of patients. “N/A” means that a dose cannot be eliminated before treating 3 evaluable patients. After the trial is completed, we will select the MTD based on isotonic regression [38]. This computation is implemented by the “Estimate MTD” tab of the BOIN Design Desktop Program [41]. Notably, each cohort of 3 patients will consist of 3 new patients. Therefore, dose escalation or de-escalation is interpatient (or, more precisely, intercohort), not intrapatient in nature.

Considering the low disease prevalence of CP, including referral bias at academic centers, we chose to avoid the use of eligibility criteria that would narrow the potential recruitment pool. In this phase 1 trial, in which safety, tolerability, and feasibility are the primary outcomes of interest, we propose including all patients with suspected or definitive CP if the above inclusion and exclusion criteria are met. Similarly, although there may be potential variability in patients because of the etiology, duration of CP, or other features of the disease, it is impractical to impose more stringent eligibility criteria during this early phase of the investigation. Doing so would substantially deplete the recruitment pool for this orphan disease and would not be feasible or scientifically justified.

**Figure 1 figure1:**
[figure not shown]
Bayesian optimal interval (BOIN) schema. The BOIN schema is a model-assisted dose-finding design that can be used to determine the maximum-tolerated dose (MTD) of a study drug based on safety or the optimal biological dose (OBD) based on safety and efficacy. DLT: dose-limiting toxicity.

**Table 1 table1:** Dose-escalation or de-escalation rule for the Bayesian optimal interval design.

Actions	The number of patients treated at the current dose														
	1	2	3	4	5	6	7	8	9	10	11	12	13	14	15
Escalate if the number of DLT^a^ is ≤	0	0	0	0	1	1	1	1	2	2	2	2	3	3	3
De-escalate if the number of DLT is ≥	1	1	2	2	2	3	3	3	4	4	4	5	5	6	6
Eliminate if the number of DLT is ≥	N/A^b^	N/A	3	3	4	4	5	5	5	6	6	7	7	8	8

^a^DLT: dose-limiting toxicity.

^b^N/A: not applicable.

### Drug Dispensing and Compliance

In this phase 1 trial, all enrolled participants will receive the active drug lacosamide. There is no placebo group, and there is no blinding to the treatment or dose received. Following the initial drug purchase, the investigational drug service at each participating institution will purchase additional disbursements on an as-needed basis, depending on patient recruitment. Participants will be provided with drug diaries, which will be reviewed for compliance at the end of the study at the final in-person visit. Patients who miss a dose (defined as beyond 2 hours of the patient’s typical drug administration time) will not be instructed to take it later on the same day. Patients will be informed not to take missed doses on the subsequent day (ie, the patient should not take more than the prescribed daily dose).

### Study Visits

A screening visit for eligibility in person or via telephone will occur at 7 to 30 days prior to enrollment. There will be 2 in-person study visits. During study visit 1 on day 0, baseline study assessments and questionnaires will be completed in person. Drug treatment days will then occur from days 1 to 7. During study visit 2 on day 8 (with a 3-day window), following completion of the 7-day drug treatment period, participants will have a face-to-face clinic visit, where similar assessments and questionnaires will be completed, as per the study calendar (Table 2). Participants will return all unused drugs during this visit for disposal and to monitor compliance.

**Table 2 table2:** Study calendar.

		Screening visit, from 7 to 30 days	Enrollment visit, day 0	Treatment days 1-7	Follow-up visit, day 8 (+3-day window)
**Required assessments**					
	Informed consent	✓			
	Medical history^a^		✓		
	Height and weight		✓		
	Physical examination		✓		✓
	Vital signs		✓		✓
	ECOG^b^ performance status	✓	✓		✓
	EKG^c^	✓			✓
	Blood chemistries^d^	✓			✓
	Hemoglobin, absolute neutrophil count, and platelets	✓			✓
	Urine pregnancy	✓	✓		
	Medication assessment^e^	✓	✓		✓
	Adverse event assessment		✓		✓
**Questionnaires**					
	Physician questionnaire		✓		
	Study coordinator questionnaire		✓		✓
	Patient questionnaire (VAS^f^, BPI^g^, PROMIS^h^, and COMPAT^i^)	✓	✓		✓
	Medication diary	✓	✓		✓

^a^Medical history and establishment of suspected or definite chronic pancreatitis diagnosis may occur at any time before trial entry.

^b^ECOG: Eastern Cooperative Oncology Group.

^c^EKG: electrocardiogram.

^d^Will include at a minimum: electrolytes, glucose, blood urea nitrogen, creatinine and creatinine clearance, calcium, and hepatic function panel.

^e^Will include detailed use of rescue pain medications and opioids use.

^f^VAS: Visual Analog Score.

^g^BPI: Brief Pain Inventory.

^h^PROMIS: Patient-Reported Outcomes Measurement Information System.

^i^COMPAT: Comprehensive Pain Assessment Tool for Chronic Pancreatitis.

### Study Measurements

A site gastroenterologist will review the complete medical history, including medications (particularly opioid use), Eastern Cooperative Oncology Group performance status, physical examination (including vital signs, height, and weight), EKG, and laboratory test results. A site research nurse will collect up to 35 mL of fasting blood using standard protocols. Given the safety or risk protocol of lacosamide and to satisfy inclusion and exclusion criteria, the blood specimens are considered routine safety laboratories and will include electrolytes, glucose, blood urea nitrogen, creatinine, creatinine clearance, calcium, and a hepatic function panel.

The patient, nurse coordinator, and physician case report forms (CRFs) will be completed before study entry. This will be based on a similar CRF currently used in PROCEED. Completion of these forms before enrollment will allow confirmation that the patient is eligible for the study. We will obtain approval from the single-center IRB to share data between protocols with the patients’ consent. An additional CRF will be completed by the nurse coordinator in collaboration with the site-specific principal investigator at the follow-up study visit, documenting all side effects noted during the drug treatment phase according to Common Terminology Criteria for Adverse Events (version 5.0).

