### Lacosamide

Lacosamide is a Schedule V controlled substance approved by the FDA for the management of seizure disorders. A controlled substance is a drug or other substance that is tightly controlled by the government, because it may be abused or cause addiction. All controlled substances in the United States are classified into 5 schedules. Schedule V drugs, including lacosamide, have the lowest potential for misuse and addiction compared with those in other schedules. Although it has been used off-label to treat pain resulting from nervous system damage, this medication is not FDA approved for the management of abdominal pain. Currently, it is being used to treat abdominal pain for research only. There may or may not be benefits for participants in this study. The participant will be closely followed by a study coordinator and site investigator during participation. Although the actual drug therapy will only last for 7 days, the participant may experience improved control of their abdominal pain symptoms during the study. Future patients may also benefit from what is learned in this study.

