**Treatment days 1 to 7**
The lacosamide tablets can be stored at room temperature. Patients will take lacosamide by mouth, 2 times a day, approximately 12 hours apart. They will be asked to try and take the tablets at the same time on each of the 7 days of the study. The tablets may be consumed with or without food. Patients will be asked to swallow the tablets whole with a glass of water or any other liquid of their choice and not chew them.Patients will be asked to complete daily medication diaries for all medications taken for pain, including the study drug.

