**Follow-up visit on day 8**
Patients will be asked to complete 4 questionnaires related to pain and how it affects their daily life.They will be asked about any health problems they may be experiencing.They will be asked what medications they have taken, including all prescriptions and nonprescription medications from the enrollment visit day 0.Their vital signs will be recorded.They will have a physical examination.Blood (approximately 7 teaspoons) will be collected for routine safety investigations. They will need to fast before the blood is collected.They will have an electrocardiogram test performed to measure the electrical function of their heart.They will return any leftover study drug doses to this visit, in the original bottles.

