### Summary of Known Potential Risks With Study Medication

#### Side Effects

A complete list of reported side effects from lacosamide trials and postmarketing experience can be found in the medication insert and Amneal Pharmaceuticals website [42]. The common side effects of lacosamide at doses in the range of 200 mg to 400 mg include dizziness (25%), ataxia (6%), fatigue, nausea, diplopia, headache, or tremor (12%-17%). Severe side effects such as cardiac rhythm or conduction abnormalities (first-degree arteriovenous block and atrial fibrillation or flutter, 0.5%) and suicidal ideation or behavior (0.2%) are rare. Case reports have been published regarding episodes of syncope and hypersensitivity reactions.

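### No symptom record or contact is scheduled during dosing (days 1-7), so severe symptoms that resolve before the day 8 (+3) visit reach the DLT count only through recall or spontaneous report

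*Protocol article*

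**What the plan says.** - **When adverse events are assessed.** In Table 2 (study calendar) the row "Adverse event assessment" is ticked for enrollment (day 0) and for the follow-up visit (day 8, +3 days). The column for treatment days 1-7 is blank.
- **What is recorded daily.** Textbox 2, for days 1-7: "Patients will be asked to complete daily medication diaries for all medications taken for pain, including the study drug". Under Drug Dispensing and Compliance, the diaries are reviewed for compliance.
- **How side effects are documented.** Under Study Measurements, the nurse coordinator and the site investigator complete a form "at the follow-up study visit, documenting all side effects noted during the drug treatment phase", graded by CTCAE version 5.0.
- **What patients are asked on day 8.** Textbox 3 gives a look-back period for medicines: "They will be asked what medications they have taken, including all prescriptions and nonprescription medications from the enrollment visit day 0". For symptoms it says: "They will be asked about any health problems they may be experiencing". Examination, vital signs, blood tests and an electrocardiogram are also done.
- **Later contact.** Textbox 3 adds a telephone visit on day 21, which also asks about health problems.
- **General statement.** The Lacosamide section says: "The participant will be closely followed by a study coordinator and site investigator during participation". It gives no contact times.
- **What depends on it.** Under Objectives and End Point a DLT is a grade 3 or 4 toxicity. Each patient counts once, as having had a DLT or not, and that count is read against Table 1.

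**The concern.** The DLT count is the only input to each dose decision. Day 8 blood tests, electrocardiogram and examination can find toxicity that is still present. They cannot recover a symptom that came and went during the dosing week. The Side Effects section lists symptoms of that kind for doses of 200 to 400 mg: "dizziness (25%), ataxia (6%), fatigue, nausea, diplopia, headache, or tremor", and it mentions case reports of syncope. These frequencies are not split by grade, so they do not say how many would be DLTs. They do show that the expected toxicity is largely symptomatic.

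Grading is exposed as well as capture. A DLT starts at grade 3, so a severe episode recalled as milder than it was is lost to the count just as a forgotten one is.

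**Working it through.** **1. Reproduce Table 1.** Inputs: target DLT rate 0.30 and cohorts of 3 (Investigational Plan). With the usual BOIN defaults, φ1 = 0.6 × 0.30 = 0.18 and φ2 = 1.4 × 0.30 = 0.42:

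- escalation boundary = ln(0.82/0.70) / ln[(0.30 × 0.82)/(0.18 × 0.70)] = 0.2365
- de-escalation boundary = ln(0.70/0.58) / ln[(0.42 × 0.70)/(0.30 × 0.58)] = 0.3585
- eliminate when the posterior probability that the DLT rate exceeds 0.30 is above 0.95, with a uniform prior

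All three rows of Table 1 are reproduced for every number of patients from 1 to 15. The rule itself is correct; the point concerns what is fed into it.

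**2. Interval to the visit.** For an event on days 1-7, a visit on day 8 falls 8 − 7 = 1 to 8 − 1 = 7 days later. At the end of the window (day 11) the longest interval is 11 − 1 = 10 days.

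**3. Effect of one missed DLT.** Compare the action at count k with the action at k − 1. The action changes at three values of k: one above the escalation limit (stay becomes escalate), at the threshold in the row "De-escalate if the number of DLT is ≥" (de-escalate becomes stay), and at the elimination threshold (eliminate becomes de-escalate).

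| Patients at dose | Escalate at or below | De-escalate at or above | Eliminate at or above | True counts at which one missed DLT changes the action |
|---|---|---|---|---|
| 3 | 0 | 2 | 3 | 1, 2, 3 |
| 6 | 1 | 3 | 4 | 2, 3, 4 |
| 9 | 2 | 4 | 5 | 3, 4, 5 |
| 12 | 2 | 5 | 7 | 3, 5, 7 |

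Every change is towards higher exposure. All three apply at 200 and 300 mg/day. At 400 mg/day there is no higher dose to escalate to, and at 100 mg/day no lower dose to de-escalate to.

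**4. Sensitivity, by assumption only.** Let s be the fraction of all DLTs that is captured. The document gives no value for s. At a true DLT rate of 0.30, the chance of seeing 0 of 3, and so escalating, is (1 − 0.30 s)³:

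| s | Chance of escalating after 3 patients |
|---|---|
| 1.0 | 0.343 |
| 0.9 | 0.389 |
| 0.8 | 0.439 |
| 0.7 | 0.493 |
| 0.5 | 0.614 |

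A simulation of the design (10,000 runs per scenario, four doses, cohorts of 3, at most 24 patients, stop at 15 on a dose) gives the probability of selecting the correct dose. The scenarios are assumed:

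| Assumed DLT rates, four doses | Correct dose | s = 1.0 | s = 0.8 |
|---|---|---|---|
| 0.30, 0.45, 0.55, 0.65 | level 1 | 65% | 48% |
| 0.10, 0.30, 0.50, 0.60 | level 2 | 65% | 54% |
| 0.05, 0.12, 0.30, 0.50 | level 3 | 59% | 51% |
| 0.02, 0.06, 0.12, 0.30 | level 4 | 76% | 88% |

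The last row improves only because missed DLTs push selection upwards and the top dose happens to be correct. With s = 1.0 there is no effect. Only symptoms that resolve before the visit are at risk, so s for all DLTs together may be close to 1.

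**The case against.** The strongest reply is that the protocol already looks back. The form described under Study Measurements is meant to cover the whole treatment phase, and an effect entered there need not have been first noted at the visit. The present-tense question in Textbox 3 is lay wording that also appears for day 0 and day 21, so it does not define the recall period. This stands: the treatment phase is not undocumented. The weakness is the source of the information for symptoms that have resolved, not the absence of a form.

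Other replies also have weight:

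- The blank column in Table 2 proves little alone, because it leaves the daily diary unticked too. The point rests on the diary description, the form and the day 8 question read together.
- The promise of close follow-up may mean contact in practice, and instructions to telephone the site may stand in the full protocol, form or consent document.
- Grade 3-4 events in the past 7 to 10 days are usually remembered, and missed tablets in the diary could prompt a question.

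Two stronger readings are tempting, and the document supports neither. A reader might infer that adverse events are sought only on day 0 and day 8. The day 21 call contradicts that, although it comes later still and does not cover dosing as it happens. A reader might also infer that the DLT count fails without dated entries. It does not: the count is yes or no per patient, and onset dates do not enter it.

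**Conclusion.** The point holds in a limited form. In the text shown, nothing scheduled on days 1-7 records symptoms, so symptomatic grade 3-4 events that resolve before day 8-11 depend on recall or spontaneous report. One such event missed or under-graded near a Table 1 boundary moves the decision towards higher exposure. That follows from Table 1 and the visit window without further assumptions.

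How often it would happen cannot be derived. The sensitivity figures show direction and scale under assumed capture. A reader might take them as an expected bias in the selected dose, but no capture rate in the document supports that. The size is unknown and probably modest. This is a cheap improvement to a workable plan; it does not invalidate the design.

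**What to change.** 1. Add one line per day to the diary that patients already complete on days 1-7: any new problem, and whether it limited self-care. Its value is capture and a severity note made at the time; the date is secondary.
2. Have the coordinator and investigator review these lines when they grade DLTs at the day 8 visit.
3. Word the day 8 health-problem question as covering the period since day 0. This matches the look-back already used for medicines and the scope of the side-effect form.

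The cost is one diary line and one reworded question, with no extra visit. The downside is that more mild events will be recorded. A short coordinator call during the dosing week is optional, at most 24 calls in all (one per patient), and is not needed for the fix.

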### Safety or Risk Issues

Lacosamide is a Schedule V medication available in tablet, oral solution, and injectable forms. In this study, only the tablet form will be used, and this is available in 50 mg, 100 mg, 150 mg, and 200 mg dosages. For simplicity in drug ordering and distribution, only 50 mg tablets will be used. Lacosamide is FDA approved as monotherapy or adjunctive therapy for partial-onset seizures, with a maximal recommended oral total daily dose of 400 mg, administered in 2 divided doses.

### Summary of Known Potential Risks With Study Medication

#### Side Effects

A complete list of reported side effects from lacosamide trials and postmarketing experience can be found in the medication insert and Amneal Pharmaceuticals website [42]. The common side effects of lacosamide at doses in the range of 200 mg to 400 mg include dizziness (25%), ataxia (6%), fatigue, nausea, diplopia, headache, or tremor (12%-17%). Severe side effects such as cardiac rhythm or conduction abnormalities (first-degree arteriovenous block and atrial fibrillation or flutter, 0.5%) and suicidal ideation or behavior (0.2%) are rare. Case reports have been published regarding episodes of syncope and hypersensitivity reactions.

#### Prior and Concomitant Medications or Procedures

Relevant information about all concomitant drugs (including prescribed, over-the-counter, or herbal preparations) taken before and during the trial and any dose or dose regimen changes that occur during the trial will be recorded in the source documents and case report form. Owing to the potential drug-to-drug interaction with other CYP3A4 or CYP2C9 inhibitors that may interfere with lacosamide levels, patients taking medications that may interfere with lacosamide metabolism will be monitored carefully. Furthermore, patients taking medications that affect cardiac conduction (eg, sodium channel blockers, β-blockers, and calcium channel blockers), including those that prolong the PR interval, will be carefully observed. We will obtain an EKG before beginning drug therapy and at the end of treatment**.**

The study principal investigators serve as the medical monitors for this trial, overseeing all aspects of the trial, including management of source documentation, adverse event collection, adverse events and protocol deviation reporting, interaction with the Data and Safety Monitoring Board (DSMB), and the creation of corrective and preventive action plans, when necessary. The DSMB will meet to review the study conduct and data relating to safety and efficacy to ensure the continued scientific validity and merit of the study. Following recruitment of the first study participant, summaries will be submitted monthly and reviewed quarterly by the DSMB and will follow the established CPDPC protocols.

### Statistical Plan and Analysis

A sample size of 24 was determined and calibrated based on the simulation such that the phase 1 trial has reasonable accuracy (>60% probability) to correctly identify the MTD across a set of practically plausible scenarios. We will use descriptive statistics to summarize the demographic and clinical characteristics of the patients. Safety data will be tabulated by the grade and type of toxicity using descriptive statistics, including mean, SD, and 95% CI. The reduction in pain scores will be summarized by the dose using the mean and 95% CI. As an exploratory analysis, *t* test (2-sided) or Wilcoxon rank-sum test will be used to compare the reduction in pain scores between the doses. The recruitment and dropout rates will be calculated for all patients and by dose and used to determine the feasibility of the treatment. Although the data generated will not have a comparator group (ie, no placebo), these will be helpful in understanding the variability of responses in patients with suspected or definite CP, which in turn will be useful for sample size calculation for a follow-up trial.

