### Patient Eligibility

Relevant to STTEPP, PROCEED study participants are divided into subcohorts to distinguish the natural history of different disease presentations at the time of admission into the cohort [34]. In STTEPP, we will leverage the resources of the CPDPC by approaching participants already enrolled in PROCEED. This approach will facilitate timely accrual, as these participants have demonstrated an interest in research and willingness to participate in CPDPC studies. Although all participants must meet the criteria for diagnosis of suspected or definite CP as per PROCEED definitions [34], study enrollment will not be limited to participants participating in PROCEED. The STTEPP inclusion and exclusion criteria are listed in Textboxes 4 and 5, respectively.

Inclusion criteria.Written informed consent and Health Insurance Portability and Accountability Act (HIPAA) authorization for release of personal health informationAge ≥18 years at the time of informed consentSuspected (YELLOW 2 or 3) or definite (RED) diagnosis of chronic pancreatitis, as per the Consortium for the Study of Chronic Pancreatitis, Diabetes, and Pancreatic Cancer’s *Prospective Evaluation of Chronic Pancreatitis for Epidemiologic and Translational Studies* (PROCEED) study definition with ongoing symptoms of abdominal painPatients must be maintained on an opioid (except methadone or suboxone) for 4 weeks before enrollment for the treatment of abdominal pain related to pancreatitis, with a daily morphine equivalent dose of 20 mg to 120 mg.Ongoing symptoms of abdominal pain even with opioid use (Visual Analog Score and Brief Pain Inventory average score ≥4, at enrollment)Eastern Cooperative Oncology Group performance status of 0 to 2 (Oken et al [35])Ability to swallow and tolerate oral tabletsFemales of childbearing potential must have a negative pregnancy testThe following laboratory parameters must be met: white blood cell count ≥3.0 K/mm^3^, absolute neutrophil count ≥1.5 K/mm^3^, hemoglobin ≥9 g/100 ml, platelets ≥75 K/mm^3^, creatinine ≤1.5 mg/100 mL, bilirubin ≤1.5 x upper limit of normal (ULN), aspartate transaminase ≤3 ULN, alanine transaminase ≤3 ULN; normal PR interval on baseline 12-lead electrocardiogram.

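### The exploratory comparison of pain reduction between doses uses unadjusted two-sample tests on groups that may hold 3 patients; one baseline-adjusted model with pooled variance would serve better

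*Protocol article*

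**What the plan says.** All references are to the protocol article. Statistical Plan and Analysis gives two statements on pain by dose. The first is descriptive: "The reduction in pain scores will be summarized by the dose using the mean and 95% CI". The second, introduced by "As an exploratory analysis", is that a two-sided t test or "Wilcoxon rank-sum test will be used to compare the reduction in pain scores between the doses". The section names no baseline covariate, no pooling of variance across doses and no use of dose order. It adds that the results should show how variable responses are and help to size a follow-up trial.

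The group sizes follow from Investigational Plan, Intervention, and Treatment Regimen: "We will enroll and treat patients in cohorts of size 3"; "The target DLT rate for MTD is 0.3, and the maximum sample size is 24"; and an instruction to "stop the trial if the number of patients treated at the current dose reaches 15". Doses run from 100 to 400 mg/day in steps of 100, which gives four ordered levels, and each cohort consists of new patients. Table 1 escalates when none of 3 patients has a dose-limiting toxicity. Table 2 schedules the pain questionnaires at screening, day 0 and day 8.

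**The concern.** The dose-finding rule allocates patients unevenly, and it leaves several doses with a single cohort when toxicity is low, which is what the article anticipates. Two-sample tests and stand-alone intervals are at their weakest there. Each uses only the patients in the groups concerned, so an interval for a dose with 3 patients rests on 2 degrees of freedom if that dose's own SD is used. A plain change score also leaves variance in the outcome that the day-0 score could explain.

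What is at stake is modest but real. These are the trial's only data on pain by dose, and the article wants to use their variability to plan phase 2. A variance estimated from 3 patients is too imprecise for that.

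**Working it through.** **Plan's own figure.** There is none to reproduce for the pain comparison. The sample size of 24 is tied to identifying the maximum tolerated dose (MTD), not to pain. All 15 columns of Table 1 reproduce with the usual Bayesian optimal interval settings for a target of 0.3, so the allocations below follow the plan's own rule.

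**Group sizes.** With no dose-limiting toxicity, each of the first three levels takes one cohort and the rest go to level 4: 3 + 3 + 3 + 15 = 24. Both the overall maximum and the cap of 15 are then reached together. In simulated trials:
- With assumed toxicity rates of 2%, 4%, 8% and 12%, mean allocation is 3.2/3.5/4.2/13.0, and 99.5% of trials have at least one dose with exactly 3 patients.
- With the MTD at level 4, 3, 2 or 1, that share is about 94%, 87%, 53% and 26%.

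**Floor of the rank-sum test.** The smallest exact two-sided p (untied data) is 2/C(n1+n2, n1).
- 3 vs 3: 2/20 = 0.10
- 3 vs 6: 2/84 = 0.024
- 3 vs 15: 2/816 = 0.002

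Under 3/3/3/15, three of the six dose pairs are 3 vs 3.

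**Interval width at n = 3.** Half-width = t(0.975, df)/√3, in SD units.
- Own SD, 2 df: 4.303/1.732 = 2.48
- Pooled over four doses, 24 − 4 = 20 df: 2.086/1.732 = 1.20

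**Precision of the SD itself.** The 95% CI multipliers are √(df/χ²) at the two tails.
- 2 df: 0.52 to 6.3 times the estimate
- 20 df: 0.77 to 1.44 times the estimate

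**Power.** The article gives no SD, correlation, effect or significance level. Assumed: SD 2 at each visit, correlation r = 0.5, two-sided 0.05, allocation 3/3/3/15, and 2.1 points between levels 1 and 4 (0.7 per level if linear).
- Variance of change = 2·SD²·(1 − r) = 2·4·0.5 = 4, so the SD of change is 2.
- Residual variance given day-0 score = SD²·(1 − r²) = 4·0.75 = 3. The ratio is 4/3 = 1.33.
- Planned t test, level 1 vs 4: noncentrality = (2.1/2)·√(3·15/18) = 1.05·1.581 = 1.66 on 16 df, which gives power of about 34%. Simulation runs gave 33% to 35%.

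| Analysis, level 1 vs 4 | Power by simulation |
|---|---|
| Planned t test on reduction | about 33% |
| Day-8 score on day-0 score and dose as factor | 43% |
| Same with a linear dose term, linear effect | 51% |
| Linear dose term, effect flat from level 2 | 29% (planned t test in the same run 35%) |

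With no effect, the models reject about 5% of the time. The factor comparison of levels 1 and 4 does not depend on the means at levels 2 and 3, so a plateau does not weaken it. For this 3 vs 15 pair the gain in power comes mainly from baseline adjustment, since the t test already has 16 df. Pooling matters most for the doses with 3 patients.

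**The case against.** The strongest reply is that the analysis is labelled exploratory, efficacy is a secondary exploratory objective, and no decision, stopping rule or sample size rests on these tests. That stands, and it keeps the severity low. It does not remove the point, because the article itself names the tests rather than leaving them to a later analysis plan.

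The article also does not say that each interval uses its own dose's SD, and nothing stops the team from computing a pooled SD. That stands too: the 2.48 figure is conditional on the own-SD reading.

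Several stronger readings are tempting but are not supported:
- **A reader might infer that the stated tests cannot detect a dose trend.** They can, with low power. The 0.10 floor holds only for the rank-sum test at 3 vs 3. The t test has no such floor, and 3 vs 15 can reach 0.002.
- **A reader might infer that baseline pain is ignored.** A reduction subtracts each patient's own baseline. What is missing is adjustment for it.
- **A reader might bring in regression to the mean**, because entry requires "Visual Analog Score and Brief Pain Inventory average score ≥4, at enrollment". The threshold is the same at every dose, so the expected fall is shared and does not bias comparisons between doses. With no placebo group, the proposed model would not remove it from the mean change at each dose either.
- **A reader might want screening and day-0 scores averaged as baseline.** Study Visits allows screening by telephone, so that could mix modes of assessment. The day-0 score suffices.

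**Conclusion.** The point holds as a low-severity improvement to one exploratory analysis. Two results need no assumed effect: the 0.10 floor for a 3 vs 3 rank-sum test, and the half-width at n = 3 of 2.5 SD with the dose's own SD against about 1.2 SD with pooled variance. The second takes equal variance across doses and all four levels in use with 24 patients.

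The gain in power, from about 33% to 43% with dose as a factor, rests on the assumed SD, correlation, difference, significance level and 3/3/3/15 allocation. The further rise to 51% also needs a linear dose effect. With a plateau from level 2 the linear term falls to about 29%, below the planned test at 35%, so it should not be the main analysis. Power stays modest in every case, and estimates with intervals are more useful than p values here.

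No model separates dose from order of enrollment, because doses are assigned in sequence and not at random. The toxicity endpoint, the escalation rule and the choice of MTD are unaffected.

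**What to change.** In Statistical Plan and Analysis, replace the between-dose t or rank-sum tests with one linear model per pain scale: day-8 score on day-0 score and dose as a factor, over the dose levels that enrolled patients. Report adjusted means for each dose and differences between doses, with 95% CIs from the pooled residual variance. Give the linear dose slope with its 95% CI as a supplementary estimate. State that the pooled SD, not the SD of a single dose, will inform phase 2 planning. Keep the exploratory label.

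The cost is a change of wording. Both scores are already scheduled, and no patients or visits are added. The text should also state the limits: variance is assumed equal across doses, the slope loses power if the effect plateaus, and dose is confounded with enrollment order.
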